### Legend for overall schedule

|                                                                                                                                                      |      |
|------------------------------------------------------------------------------------------------------------------------------------------------------|------|
| Standard test for CI                                                                                                                                 | XX   |
| Extra test for VertiGO! trial                                                                                                                        | XX   |
| Standard visit for CI                                                                                                                                |      |
| Extra visit for VertiGO! trial                                                                                                                       |      |
| Planning is variable                                                                                                                                 | var. |
| If response was absent at previous timepoint and no further optimized measuring techniques are available, repeated measurements will be skipped      | x*   |
| Part of CI fitting                                                                                                                                   | A    |
| Often clinically necessary                                                                                                                           | B    |
| Device deficiencies of AMP processor will only be recorded during active use, namely during VI fitting period and period of prolonged VI stimulation | C    |

Table 3. Example of the schedule for the VI fitting period (version 2)

| VI FITTING |       |                                  |                                  |                                             |                                            |           |
|------------|-------|----------------------------------|----------------------------------|---------------------------------------------|--------------------------------------------|-----------|
| Day        | 0     | 1                                | 2                                | 3                                           | 4                                          | 5         |
| Time       | 08:00 | Breakfast                        |                                  | Breakfast                                   | Breakfast                                  | Breakfast |
| 09:00      |       |                                  |                                  |                                             |                                            |           |
| 10:00      |       | Costas array-based experiment    | CI and CVI aided DVA             |                                             | Static CI aided CNC + SPIN                 |           |
| 11:00      |       | First fitting - First SCC (1/2)  | First fitting - Third SCC (1/2)  | Second fitting - Second SCC (1/2)           | Combined fitting evaluation and adjustment |           |
| 12:00      |       | Break                            | Break                            | Break                                       | Break                                      |           |
| 13:00      |       | First fitting - First SCC (2/2)  | First fitting - Third SCC (2/2)  | Second fitting - Second SCC (2/2)           | Combined fitting evaluation and adjustment |           |
| 14:00      |       | Lunch                            | Lunch                            | Lunch                                       | Lunch                                      |           |
| 15:00      |       | First fitting - Second SCC (1/2) | Second fitting - first SCC (1/2) | Second fitting - Third SCC (1/2)            | Combined fitting evaluation and adjustment |           |
| 16:00      |       | Break                            | Break                            | Break                                       | Break                                      |           |
| 17:00      |       | First fitting - Second SCC (2/2) | Second fitting - first SCC (2/2) | Second fitting - Third SCC (2/2)            | Costas array-based experiment              |           |
| 18:00      |       | VBR                              | Semi-structured interview        | Familiarization with gait and balance tests | Final overall fitting check                |           |
| 19:00      |       |                                  |                                  |                                             | Static CVI aided CNC + SPIN                |           |
| Night      | Hotel | Hotel                            | Hotel                            | Hotel                                       | Hotel                                      |           |

## Legend for VI fitting and baseline testing schedules

|                      |           |  |
|----------------------|-----------|--|
| Time at the hotel    | Testing   |  |
| Time at the hospital | Fitting   |  |
|                      | Interview |  |
|                      | Free time |  |

Table 2. Example of the schedule for the baseline testing day (version 1)

| BASELINE TESTING |                                    |
|------------------|------------------------------------|
| Day              | 1                                  |
| Time             | 08:00                              |
| 09:00            | Questionnaires at home             |
| 10:00            | Perception platform                |
| 11:00            | Gait and balance tests (1/2)       |
| 12:00            | Break                              |
| 13:00            | Gait and balance tests (2/2)       |
| 14:00            | Rotatory chair                     |
| 15:00            | Lunch                              |
| 16:00            | DVA + static and dynamic aided CNC |
| 17:00            | Break                              |
| 18:00            | 3D HIT + fHIT                      |
| 19:00            |                                    |
| Night            | At home                            |

Table 4. Example of the schedule for the prolonged stimulation period

| PROLONGED STIMULATION PERIOD         |      |      |      |      |      |      |                                      |      |      |      |      |      |      |                                      |      |      |      |      |      |      |
|--------------------------------------|------|------|------|------|------|------|--------------------------------------|------|------|------|------|------|------|--------------------------------------|------|------|------|------|------|------|
| Stimulation algorithm 1 (randomized) |      |      |      |      |      |      | Stimulation algorithm 2 (randomized) |      |      |      |      |      |      | Stimulation algorithm 3 (randomized) |      |      |      |      |      |      |
| Sun.                                 | Mon. | Tue. | Wed. | Thu. | Fri. | Sat. | Sun.                                 | Mon. | Tue. | Wed. | Thu. | Fri. | Sat. | Sun.                                 | Mon. | Tue. | Wed. | Thu. | Fri. | Sat. |
| 1                                    | 2    | 3    | 4    | 5    | 6    | 7    | 8                                    | 9    | 10   | 11   | 12   | 13   | 14   | 15                                   | 16   | 17   | 18   | 19   | 20   | 21   |

| Weekly schedule |                                  |                                 |                                 |                                 |                                 |             |               |
|-----------------|----------------------------------|---------------------------------|---------------------------------|---------------------------------|---------------------------------|-------------|---------------|
| Day             | Sunday
1                      | Monday
2                     | Tuesday
3                    | Wednesday
4                  | Thursday
5                   | Friday
6 | Saturday
7 |
| Time            |                                  | Breakfast                       | Breakfast                       | Breakfast                       | Breakfast                       | Breakfast   |               |
| 08:00           |                                  |                                 |                                 |                                 |                                 |             |               |
| 09:00           |                                  | Start-of-day check C | Start-of-day check C | Start-of-day check C | Start-of-day check C |             |               |
| 10:00           |                                  | Habituation A        | Habituation                     | Habituation                     | Habituation                     |             |               |
| 11:00           |                                  | Break                           | Perception platform             | Gait and balance tests (1/2)    | Perception platform             |             |               |
| 12:00           |                                  | Head impulse tests B | Break                           | Break                           | Break                           |             |               |
| 13:00           |                                  | Lunch                           | Lunch                           | Lunch                           | Lunch                           |             |               |
| 14:00           |                                  | DVA                             | DVA                             | DVA                             | DVA + dynamic CNC               |             |               |
| 15:00           |                                  | Break                           | Break                           | Break                           | Interview                       |             |               |
| 16:00           |                                  | Rotatory chair                  | Rehabilitation                  | Rotatory chair                  | Break                           |             |               |
| 17:00           | Perception platform E | Physiotherapeutic diagnosis     | Break                           | Costas array                    | Head impulse tests B |             |               |
| 18:00           |                                  | End-of-day check D   | End-of-day check D   | End-of-day check D   | End-of-day check D   |             |               |
| 19:00           | Dinner                           | Dinner                          | Dinner                          | Dinner                          | Dinner                          |             |               |
| Night           | Hotel                            | Hotel                           | Hotel                           | Hotel                           | Hotel                           | At home     | At home       |

| Legend for prolonged stimulation period schedule            |  |   |
|-------------------------------------------------------------|--|---|
| Time at the hotel                                           |  |   |
| Testing                                                     |  |   |
| Rehabilitation                                              |  |   |
| Time at the hospital                                        |  |   |
| Interviews                                                  |  |   |
| Habituation and device check                                |  |   |
| Free time                                                   |  |   |
| Including a short fitting check if necessary                |  | A |
| 3D HIT, fHIT, simulated 3D HIT and simulated rotatory chair |  | B |
| Impedance and UCL check                                     |  | C |
| Impedance, UCL check and VAS-based list of questions        |  | D |
| Measured without CVI active                                 |  | E |

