#### 8.1.1. Main study parameters/endpoints

The primary objective is assessing the efficacy of the CVI in restoring vestibular function. This will be measured by using a set of vestibular tests, of which DVA will be the main outcome parameter. The tests that will be performed observe two vestibular-related reflex pathways: VOR (gaze stabilization) and VSR (postural balance). The VOR tests consist of the DVA test, the functional head impulse test (fHIT), the 3D video head impulse test (3D HIT) and the torsion swing test. All these tests quantify the VOR at different frequencies and at different levels of functionality. The VSR is observed based on gait and balance tests, looking at the full body response to vestibular stimulation on a functional level. Besides these tests, also the threshold of the perception of movement will be measured using the perception platform.

The main comparison will be made between the measurements done during baseline testing (VI-OFF) and the measurements done during the prolonged stimulation period (VI-ON) (see chapter 2). This will give a

Table 6: Overview of VertiGO! objectives, goals, endpoints and outcome parameters

| Objective |                       |    | Goal                          | Measurement points                                   | Outcome parameters |      |                                                                 |
|-----------|-----------------------|----|-------------------------------|------------------------------------------------------|--------------------|------|-----------------------------------------------------------------|
|           |                       |    |                               |                                                      | Type               | Test |                                                                 |
| Primary   | Prolonged daily stim. | 1a | Overall efficacy              | VI-OFF (baseline) vs VI-ON (stim. weeks)             | Prim.              | Main | DVA                                                             |
|           |                       |    | Adaption to stimulation       | VI-ON (start stim. weeks) vs VI-ON (end stim. weeks) |                    | Aux. | fHIT, 3D HIT, Torsion Swing, Gait analysis, Perception platform |

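### In the example schedules, VI-OFF DVA comes two hours later in the day and after more testing than VI-ON DVA, so time of day and test load are confounded with VI status in the main comparison

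*Protocol*

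**What the plan says.** The timetables are in Protocol 3.2. Table 2 is the baseline day (8.3.6 refers to it as table 3) and Table 4 is the stimulation week. Both are titled as examples, and 3.2 calls the schedules indicative and open to slight change.

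- **Baseline day, VI-OFF.** The 16:00 entry is "DVA + static and dynamic aided CNC". The last test slot, at 18:00, holds 3D HIT and fHIT.
- **Stimulation week, VI-ON.** DVA is at 14:00 from Monday to Thursday. The Thursday entry reads "DVA + dynamic CNC". The entry "Head impulse tests" appears twice, on Monday at 12:00 and on Thursday at 17:00. Section 8.3.6 keeps the testing schedule the same in all three weeks.
- **Main contrast.** Section 8.1.1 states: "The main comparison will be made between the measurements done during baseline testing (VI-OFF) and the measurements done during the prolonged stimulation period (VI-ON". Section 10.1 tests it with a Wilcoxon signed-rank test.
- **Adaptation contrast.** Table 6 gives it as "VI-ON (start stim. weeks) vs VI-ON (end stim. weeks", with fHIT and 3D HIT among the auxiliary outcomes.

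The protocol does not match or adjust for clock time, preceding tests or hours of stimulation on the day.

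**The concern.** DVA is read while walking on a treadmill. At baseline it comes after the whole gait-and-balance session, which includes treadmill walking at several speeds with platform perturbations and for which 8.3.1 itself collects ratings of effort and fatigue. On stimulation days it comes two hours earlier, after one printed test slot. If time of day or preceding load affects walking acuity at all, the effect enters the VI-OFF minus VI-ON difference of every patient with the same sign. It does not average out over patients, and the analysis would count it as part of the implant effect.

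A smaller issue of the same kind concerns adaptation. The first and last head impulse tests of the week are taken after very different amounts of stimulation that day. A change between them could reflect four days of use or a few more hours of use.

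**Working it through.** **1. The plan's own figure.** Section 4.4 gives logMAR 0.205 (SD 0.066) for VI inactive and 0.065 (SD 0.061) for VI active, a difference of 0.140. The stated effect size of 2.20 requires a within-patient correlation of 0.5, which is not stated but inferred:

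SD of differences = √(0.061² + 0.066² − 2 × 0.5 × 0.061 × 0.066) = 0.0636, and 0.140 / 0.0636 = 2.20.

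A noncentral-t calculation with the Wilcoxon efficiency correction then gives n = 5, as stated. The SD of 0.0636 is used in step 5.

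**2. DVA slots as printed in Tables 2 and 4.**

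| Day | Test slots before DVA | Number | DVA at |
|---|---|---|---|
| Baseline (VI-OFF) | perception platform 10:00; gait (1/2) 11:00; gait (2/2) 13:00; rotatory chair 14:00 | 4 | 16:00 |
| Monday | head impulse 12:00 | 1 | 14:00 |
| Tuesday | perception platform 11:00 | 1 | 14:00 |
| Wednesday | gait (1/2) 11:00 | 1 (uncertain) | 14:00 |
| Thursday | perception platform 11:00 | 1 | 14:00 |

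The Wednesday count is uncertain because Table 4 lists "Gait and balance tests (1/2") but shows no second half anywhere in the week; a cell may have been lost from the text. The start-of-day check and habituation are not counted as tests. The clock difference is 16:00 − 14:00 = 2 hours. Lunch comes directly before DVA on both kinds of day.

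**3. What the paired test estimates.** For each patient, the VI-OFF minus VI-ON difference equals the implant effect plus the effect of slot (clock time and preceding load). Every VI-OFF value has one slot position and every VI-ON value the other, so the two terms cannot be separated. Randomising the order of the three algorithms does not help, because all three weeks use the same timetable.

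**4. Head impulse tests.** Habituation starts at 10:00. Monday: 12:00 − 10:00 = about 2 hours of stimulation. Thursday: 17:00 − 10:00 = about 7 hours. The gap is about 5 hours. The other repeated tests are matched within the week: DVA at 14:00 on all four days, rotatory chair at 16:00 on Monday and Wednesday, perception platform at 11:00 on Tuesday and Thursday.

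**5. Scale, for illustration only.** The documents give no slot effect, so the shifts below are assumptions. With no true implant effect, normally distributed differences with SD 0.0636 and an exact two-sided signed-rank test at 0.05, simulation gives these rejection rates:

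| Assumed shift (logMAR) | n = 8 | n = 13 |
|---|---|---|
| 0 | 0.04 | 0.05 |
| 0.01 | 0.05 | 0.08 |
| 0.02 | 0.10 | 0.17 |
| 0.04 | 0.29 | 0.53 |
| 0.06 | 0.57 | 0.86 |

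A shift of 0.02 is 0.02 / 0.14 = 14% of the planned difference. The test is two-sided, so these rates apply to a shift in either direction. A shift against VI-ON would instead hide benefit: at 0.06, a true difference of 0.14 would appear as 0.08, and the simulated power at n = 8 would fall from above 0.99 to 0.80.

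**The case against.** The strongest reply has four parts.

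- **The timetables are examples.** They are indicative, with generous margins and frequent breaks. Section 8.3.6 puts the hospital day at roughly 08:30 to 17:30, while Table 4 runs to an 18:00 check, so the clock rows are approximate. This stands, and it makes the repair easy. It does not supply a matching rule, and 8.3.6 points to these tables as the schedules.
- **Tiredness at baseline is not shown.** A reader might infer that VI-OFF is measured in a tired patient and VI-ON in a fresher one, so that the bias favours the implant. The documents do not support that. Two of the four earlier baseline slots are seated tests. VI-ON days add a device check, habituation and hours of active stimulation before DVA; 6.4.6 mentions tiredness after earlier adjustment of settings and possible nausea in prolonged use. The direction is open.
- **There is a partial control.** Static acuity is measured as a reference (8.3.1), and the planning data were normalised to it (4.4). It may absorb general visual tiredness, but not fatigue of gait or balance.
- **One baseline day cannot match everything.** It holds tests that the stimulation week spreads over four days. This is true, but DVA, gait (1/2) and the rotatory chair can be matched together without breaking an existing match.

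Section 10 also calls the trial exploratory. That limits the claims to be drawn from it, but DVA remains the main outcome and 10.1 still tests it formally.

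**Conclusion.** The point holds as a systematic, avoidable confounding of time of day and preceding test load with VI status in the main DVA comparison: 16:00 against 14:00, and four preceding test slots against one as printed, with the Wednesday count less certain. Its size and direction are unknown from the documents. The rejection rates above rest wholly on assumed shifts and do not show an inflated error rate in this trial.

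The secondary point is narrower. The start-versus-end contrast for 3D HIT and fHIT mixes across-day adaptation with about five hours' difference in same-day stimulation. A reader might infer that this contrast is uninterpretable, or that adaptation in general is affected. Neither follows: the contrast is confounded and can be reported with that limitation, and neither DVA adaptation nor the DVA comparison of algorithms is affected by clock time, because DVA is at 14:00 on every stimulation day.

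**What to change.** **Main point.** Reorder Table 2 to mirror the stimulation-week slots, for example: perception platform 10:00; gait (1/2) 11:00; break 12:00; lunch 13:00; DVA with CNC 14:00; gait (2/2) 15:00; rotatory chair 16:00; break 17:00; 3D HIT and fHIT 18:00. DVA, gait (1/2) and the rotatory chair then have the same clock times as in Table 4, and the slots before DVA fall from four to two. The cost is a denser early afternoon, with three test slots in a row after lunch. No test or visit is added, and 3.2 already allows slight changes to the schedules.

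**Secondary point.** Either exchange Monday's 12:00 head impulse slot with the 17:00 physiotherapeutic diagnosis, or keep the timetable and state the limitation when that contrast is interpreted. The exchange matches Thursday's 17:00 and comes within one hour of the 18:00 baseline test, but the first head impulse measurement of the week is then taken after about 7 hours of stimulation. Exchanging Thursday's perception platform and head impulse slots is not advised: it leaves 11:00 against 12:00 for the head impulse tests and creates a six-hour mismatch (17:00 against 11:00) for the perception platform.

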## 4. STUDY POPULATION

### 4.1. Population (base)

The study population consists of capacitated adults who have (1) disabling symptoms of BV and (2) severe SNHL in at least the ear to be implanted. As part of standard clinical routine at the ENT department of the MUMC+, every patient that is believed to suffer from a balance disorder or is candidate for cochlear implantation undergoes a screening of his or her vestibular function by means of bilateral caloric test. Patients who appear to be eligible for and interested in participating in the next VI study are asked for consent to be put on a “VI-waiting list”. This list now includes hundreds of patients who are potentially fit for inclusion in this trial. The VI-waiting list will serve as the population base from which patients will be recruited.

In previous VI-related studies, patient inclusion has not been an issue. If it does turn out that including 8 patients out of the MUMC+ database proves problematic, potential patients might be sourced via collaboration with the Antwerp University Hospital (UZA). Patients from the UZA will be informed by their own ENT specialist who then refers them to a member of the research team for further information. All trial related activities will be conducted within the MUMC+.

